## 1. Introduction

In Europe, the yearly occurrence of cardiogenic shock resulting from cardiac arrest is estimated to range between 67 and 170 cases per 100,000 inhabitants [1]. When considering shock attributed to heart failure as well, the number rises to approximately 500,000 individuals [2]. However, poor overall survival persists, especially after cardiac arrest with a survival rate upon hospital discharge ranging from 0% to 18%, with an overall average of 8% [1].

The integration of percutaneous, mechanical, extracorporeal support for oxygenation and circulation serves as a secondary line of treatment for achieving hemodynamic stabilization [3,4] and veno-arterial extracorporeal membrane oxygenation (VA–ECMO) serves as a rescue therapy for patients experiencing shock that is unresponsive to conventional resuscitation efforts [3,5,6,7]. It functions as a bridging intervention, ensuring the maintenance of organ perfusion while the underlying cause of the shock is identified and addressed [3]. This treatment approach has demonstrated encouraging survival rates falling within the range of 20% to 30% [3,8,9].

Conditions that may necessitate ECMO support, such as cardiogenic shock or cardiac arrest, exhibit a shared pathogenetic mechanism of clinical deterioration, characterized by hyperinflammation [10,11,12]. This systemic inflammatory response syndrome (SIRS), which occurs to varying degrees in the majority of patients on ECMO support, is typically not infection-driven but rather a response to tissue injury associated with the underlying condition [12]. Furthermore, the ECMO support itself can trigger and sustain an inflammatory response through diverse mechanisms, including the contact between blood cells and molecules with the artificial surfaces of tubing, rotor, and oxygenator within the ECMO circuit [12,13]. Due to SIRS, the consequent development of multiorgan dysfunction syndrome (MODS) leads to a significant reliance on inotropic support. The administration of high doses and/or multiple different inotropes not only fails to alleviate tissue hypoxia and systemic inflammation but often exacerbates them, ultimately leading to increased mortality rates [12,14,15,16,17].

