#### 2.7.2. Secondary Endpoints of the Study Are as Follows (Selection)

Duration of renal replacement therapy (continuous venovenous hemodialysis (CVVHD)), mechanical ventilation, ECMO therapy, inotropic/vasopressor treatment 7 and 30 days after the beginning of the intervention.

30–day mortality defined as mortality, in the hospital or anywhere after discharge, within 30 days after the beginning of the intervention.

Changes in mediators/markers of inflammation, myocardial damage, oxidative stress, myocardial wall stress, myocardial remodeling, kidney injury and kidney function at baseline, every 24 h during the intervention phase (up to 72 h) and on day 7 after the beginning of the intervention.

Length of stay in ICU and total length of hospital stay until discharge/transfer within 30 days after the beginning of the intervention.

Echocardiographic parameters of left and right ventricular function at baseline, every 24 h during the intervention phase (up to 72 h) and on day 7 after the beginning of the intervention.

Marker of hemolysis every 24 h under ECMO treatment (up to 72 h) after the beginning of the intervention.

Implantation of an active assist device or heart transplantation assessed on day 30 after the beginning of the intervention.

Simplified acute physiology score (SAPS) II, acute physiology and chronic health evaluation (APACHE) II; sequential organ failure assessment (SOFA) score at baseline, every 24 h during the intervention phase (up to 72 h) and on day 7 after the beginning of the intervention.

EQ–5D–3L questionnaire including EQ VAS (visual analogue scale), rehospitalization due to heart failure measured 30 days after the beginning of the intervention.

Neurological outcome: mRS (modified Rankin Scale), incidence of apoplexy, Glasgow Coma Scale (GCS), neuron-specific enolase (NSE), S–100, cerebral performance category (CPC), if clinically necessary and available: Computed tomography (head CT)/medianus somatosensory evoked potential (SEP) at baseline, every 24 h during the intervention phase (up to 72 h), on day 7 and on day 30 after the beginning of the intervention.

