#### 2.12.2. Statistics

The primary outcome analysis will involve comparing the experimental group receiving CytoSorb^®^ with the control group receiving standard care (without CytoSorb^®^), focusing on the differences in the mean Inotropic Score (IS) at 72 h post-implantation. The primary analysis will encompass the full analysis set, including all patients who were randomized and received treatment, following the intent-to-treat (ITT) principle. Sensitivity analyses are planned in the per-protocol (PP) analysis set. A linear model will be fitted for the primary endpoint with treatment and baseline IS as fixed effects. The confirmatory analysis will be performed at a significance level of 5%. The mean difference of the primary endpoint will be estimated within the model and will be reported with 95% confidence interval. Categorical endpoints will be compared by Chi-square test/Fisher’s exact test between groups. According to the data distribution, two-sided independent samples *t* test or Mann–Whitney U test will be applied for continuous endpoints. Adequate descriptive statistics will be used to summarize the data in each group. All secondary analyses will be performed exploratively, i.e., without adjustment for multiplicity. Safety analyses will be run in the safety population to be defined in the protocol; these analyses will summarize and tabulate all observed safety events including a measure of uncertainty (i.e., 95% confidence intervals).

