## 3. Discussion

Despite the growing utilization of ECMO in various life-threatening acute conditions [12,30,31,32], significant progress in the field of mechanical circulatory support and critical care, the rates of morbidity and mortality among ECMO patients continue to be alarmingly high [12]. The ICU mortality rate for our ECMO patients is approximately 80%.

The effectiveness of CytoSorb^®^ remains a subject of controversy [33]. Triple-blinded, randomized trials investigating the acute hemodynamic, echocardiographic, immunological, and cellular effects of VA-ECMO with the concurrent use of an adsorber to mitigate or potentially prevent an associated inflammatory response in patients with cardiogenic shock have not yet been conducted. ECMOsorb aims to assess the effectiveness of CytoSorb^®^ through a triple-blinded, randomized trial involving a larger cohort of patients with cardiogenic shock and VA-ECMO. The trial will focus on evaluating a clinical endpoint associated with hemodynamic improvement. Establishing efficacy would represent an initial evidence-based advancement for this challenging patient population that is often difficult to treat.

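### Durations of organ support and length of stay are compared with no account of death, although the article implies 70–80% mortality, so an early death can count as a short duration

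*Protocol article*

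**What the plan says.** Section 2.7.2 of the protocol article defines one group of secondary endpoints as durations of renal replacement, "mechanical ventilation, ECMO therapy, inotropic/vasopressor treatment 7 and 30 days after the beginning of the intervention". A second group is "Length of stay in ICU and total length of hospital stay until discharge/transfer within 30 days after the beginning of the intervention". Thirty-day mortality is listed as a separate endpoint and is not combined with either group.

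Section 2.12.2 gives one rule for the test: "According to the data distribution, two-sided independent samples *t* test or Mann–Whitney U test will be applied for continuous endpoints". All secondary analyses are exploratory, without multiplicity adjustment.

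On expected mortality, the Discussion states: "The ICU mortality rate for our ECMO patients is approximately 80" per cent. The Introduction describes VA-ECMO as having "encouraging survival rates falling within the range of 20% to 30" per cent.

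No section turns these endpoints into support-free days, ranks death as the worst result, or treats death as a competing event.

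**The concern.** On a plain reading, each duration is a number of days, and a t test or Mann–Whitney U test compares those numbers between arms. A patient who dies on day 2 while on ECMO then contributes 2 days, which looks better than a survivor weaned on day 15. Where mortality is high, the comparison mixes two opposite ways of having a short duration.

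The matter is not peripheral. The Abstract hypothesises that lower cytokine levels let patients come off inotropes and mechanical support sooner, and the ECMO and catecholamine durations measure that most directly. Section 2.6.2 looks to the secondary objectives to bear out possible benefits of the device. A device that saves lives could appear to prolong support, and one that hastens death could appear to shorten it.

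**Working it through.** The plan gives no figure for these endpoints, so there is none to reproduce. The check uses its patient numbers and mortality figures. All times below are assumptions, because the article gives none.

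**Inputs from the article.** 54 patients, 27 per group (2.12.1); 30-day follow-up (2.3); about 80% ICU mortality at the site (Discussion); 20–30% survival, hence 70–80% mortality (Introduction).

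**How many deaths.** 54 × 0.70 = 37.8 and 54 × 0.80 = 43.2. Survivors per group: 27 × 0.20 = 5.4 to 27 × 0.30 = 8.1. Restricting the analysis to survivors would leave about 5 to 8 patients per arm, selected by an outcome that arises after randomisation.

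**Raw duration of support.** Let p be mortality, D the mean days on support among those who die (assumed to stay on support until death), and S the mean days to weaning among survivors, with D and S equal in both arms.

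- Mean duration = p·D + (1 − p)·S
- Difference, better arm minus worse arm = (p_worse − p_better) × (S − D)

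The only treatment effect is mortality of 80% versus 60%. The last column comes from a simulation with 27 per arm and 1,500 replicates: exponential death times, gamma weaning times (shape 4), both capped at day 30. It gives the share of trials with two-sided Mann–Whitney p < 0.05 and a longer mean in the better arm.

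| D | S | Mean at 80% | Mean at 60% | Difference | Significant in the wrong direction |
|---|---|---|---|---|---|
| 3 | 8 | 4.0 | 5.0 | +1.0 | 14.6% |
| 3 | 12 | 4.8 | 6.6 | +1.8 | 21.3% |
| 5 | 8 | 5.6 | 6.2 | +0.6 | 8.5% |
| 5 | 12 | 6.4 | 7.8 | +1.4 | 14.3% |
| 8 | 8 | 8.0 | 8.0 | 0 (0.04 simulated) | 3.5% |
| 8 | 12 | 8.8 | 9.6 | +0.8 | 8.0% |

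The nominal rate in one direction is 2.5%. With 80% mortality in both arms the simulation gave 2.1% to 2.7%, so the distortion does come from the mortality difference. With 70% versus 50% the wrong-direction rate was 3.9% to 19.1%, and with 80% versus 50% it was 5.1% to 39.9%.

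**Time of death alone.** Hold mortality at 80% in both arms with S = 12. Moving D from 3 to 5 changes the mean from 4.8 to 6.4 days, a difference of 0.8 × 2 = 1.6. Later death looks like longer support.

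**ICU stay, one assumed scenario.** Deaths at day 5 and survivors staying 20 days: 0.8 × 5 + 0.2 × 20 = 8 days, against 0.6 × 5 + 0.4 × 20 = 11 days. The arm with fewer deaths looks 3 days worse.

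**The alternative measure.** For means, score death as 0. Days alive and free of support to day 30 = (1 − p) × (30 − S).

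- S = 8: 0.2 × 22 = 4.4 versus 0.4 × 22 = 8.8
- S = 12: 0.2 × 18 = 3.6 versus 0.4 × 18 = 7.2
- ICU scenario: 0.2 × 10 = 2 versus 0.4 × 10 = 4

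All point the right way.

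**Its limit.** If mortality is 80% in both arms and the device only shortens weaning from S = 12 to S = 8, support-free days move from 3.6 to 4.4. That is 0.8 days, the same shift that raw duration shows (0.2 × 4). The alternative corrects direction; it does not add sensitivity to faster weaning.

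**The case against.** The strongest reply is that this is detail for the analysis plan. Section 2.7.2 is headed as a selection, section 2.12.2 gives one generic sentence on continuous endpoints, and an unseen SAP could contain a rule for death. A reader might infer that the article lays down that a death counts as a completed short stay. It does not: raw days is the plain reading of the endpoint wording, and the stay endpoint names only discharge or transfer as its end. The point still stands, because the article commits to both the form of the endpoint and the test, and neither provides for death.

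A reader might also infer that death is the main reason every one of these durations ends. That is not shown. The 80% is ICU mortality, not death on support. A patient may be weaned from ECMO or dialysis and die later, and section 2.10.2 also describes exit to transplant or an assist device. The figure describes the site's ECMO patients and is not a planning value; the exclusions in section 2.9 could lower it. The Introduction's range independently supports saying that most patients are expected to die.

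The consequences are also limited. The endpoints are exploratory, and 30-day mortality is reported separately, so opposite movements would be visible. That helps interpretation but does not repair the duration tests.

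Finally, support-free days with about 80% of patients at the worst value largely repeat mortality. That is true and is a cost of the change.

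**Conclusion.** The concern holds in a limited form. The stated endpoints and tests let an early death count as a short duration in a population where the article implies 70–80% mortality. If the device changes mortality or the time of death, the comparisons can be biased and may point the wrong way.

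The size is uncertain. For 80% versus 60% mortality, mean support is about 0 to 2 days longer in the better arm, and close to zero when those who die and those who survive have similar durations. Significant results in the wrong direction occur in about 3.5% to 21% of simulated trials, against a nominal 2.5%. The 3-day figure for ICU stay belongs to one assumed scenario and should not be read as an expected reversal. Without an effect on mortality or time of death, this mechanism produces no directional bias.

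The change should be made because these endpoints speak to the trial's own weaning hypothesis. The confirmatory comparison of the Inotropic Score at 72 h is not affected by this point.

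**What to change.** In sections 2.7.2 and 2.12.2, for the between-group comparison in all randomised and treated patients:

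- Replace each organ-support duration with days alive and free of that support to day 30, and to day 7 where the protocol already reads it.
- Replace ICU stay with days alive and out of ICU to day 30. Do the same for hospital stay only where discharge and readmission dates allow.
- Rank death by that day as the worst result, below a survivor who is still on support or still in the ICU.
- Compare by Mann–Whitney U test and present the result beside 30-day mortality.
- Keep raw durations and stays as description, split by survival status.

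ICU- and hospital-free days to day 7 should not be added: section 2.7.2 reads stay only within 30 days, and with survivors staying 20 ICU days the day-7 value would be zero for everyone. Nothing here supports extending the rule to EQ-5D.

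**Cost.** This is mainly wording. Table 1 already schedules mortality and the durations of ECMO, ventilation, dialysis and inotropic therapy, so no new visits or patients are needed. Those data come from routine records where they exist, so completeness needs checking. Hospital-free days may not be computable, because stay is followed only to discharge or transfer and rehospitalisation is captured only for heart failure. The statistical price is many ties at the worst value and a composite driven largely by mortality, so its components must be shown.

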### 2.8. Inclusion Criteria

Critically ill patients with cardiogenic shock with or without reanimation (CPR) and indication for VA–ECMO with the following mandatory requirements will be included: Systolic blood pressure < 90 mmHg, >30 min of inotropic agents and/or vasopressors to keep the blood pressure > 90 mmHg systolic, signs of left ventricular failure with pulmonary congestion and signs of end organ hypoperfusion (at least one of the following criteria: clouding of consciousness, cold, pale skin or extremities, oliguria (≤30 mL/h), serum lactate > 2.0 mmol/L, age ≥ 18 years ≤ 80 years). In order to be enrolled in the study, participants are required to provide a signed informed consent document.

### 2.9. Exclusion Criteria

Exclusion criteria are: contraindications to VA–ECMO implantation, patients with pre-existing sepsis (raised C-reactive protein (CRP), positive procalcitonin (PCT), leukocytosis, fever, positive blood cultures), shock duration > 12 h before evaluation, severe PVD (peripheral vessel disease) making ECMO–implantation impossible, aortic valve regurgitation/stenosis at least II°, age: <18, >80 years, CNS (central nervous system) disease with fixed, dilated pupils (not drug-induced), severe concomitant disease with limited life expectancy < 6 months, participation in another study, cardiopulmonary resuscitation (CPR) > 60 min, shock due to other reasons, pregnancy, HIT (Heparin-induced thrombocytopenia) positive, very low platelet counts (<20,000/μL), body weight less than 45 kg and a current immunosuppressive or immunomodulatory therapy.

### 2.10. Technology Used in the Trial

#### 2.10.1. ECMO

For the ECMOsorb trial, patients with cardiogenic shock requiring mechanical, circulatory support in form of VA–ECMO will be recruited. ECMO is a method of extracorporeal organ replacement in which the pulmonary and/or the cardiac function are partially or completely replaced. VA–ECMO in particular drains venous blood from a large–lumen vein near the right atrium through a cannula and connected tubing system and returns it via inflow into the arterial system, typically to the iliac arteries toward the aorta. Cannulas are inserted percutaneously, usually by Seldinger technique, through which blood is conveyed by means of a centrifugal pump through a membrane oxygenator and returned to the patient. During the circuit passage, the blood runs through an extracorporeal gas exchange unit where it is oxygenated, decarboxylated and warmed. ECMO represents a massive right–left shunt establishing flow rates of up to 10 L per minute depending on cannula and rotor type. The clinical result is a significant increase in blood pressure in the presence of adequate vascular resistance.

At the trial site, an ECMO from the manufacturer Getinge^®^ (Rastatt, Germany) will be used. This artificial circuit (Figure 3) consists of a preassembled, standard tubing set (BE–PLS 2050, Getinge^®^) that includes the Rotaflow RF–32 centrifugal pump (Getinge^®^, Rastatt, Germany), QUADROX^®^ oxygenator (Getinge^®^, Rastatt, Germany) and standard tubing. The system is operated via the Rotaflow console (Getinge^®^, Rastatt, Germany) mounted at the Rotaflow Sprinter Unit with heater unit HU 35 (Getinge^®^, Rastatt, Germany) and manual blender. The circuit will be established via complete lower body cannulation of femoral vessels using sheath sizes 17–21 Fr (arterial) and 19–25 Fr (venous). All patients receive an antegrade limp perfusion via an additional 7 Fr bypass cannula (CruraSave^®^ Femoral–Perfusion Set, free life medical GmbH^®^, Aachen, Germany). If additional left ventricular (LV) support is required to address persistent, insufficient cardiac output, implantation of a percutaneous microaxial pump (Impella CP^®^, Abiomed, Danvers, MA, USA) from a femoral arterial access to facilitate LV venting will be performed. An intraaortic balloon pump (IABP) will not be used.

#### 2.10.2. VA–ECMO Weaning

Initiating weaning from VA–ECMO involves an individualized strategy that requires hemodynamic stability, an improvement of left ventricular pump function and a controlled underlying cause of cardiogenic shock. Patients experiencing ongoing cardiac failure are deemed unable for weaning. A daily evaluation to assess the potential for weaning is implemented using clinical, laboratory, and echocardiographic data that either favor weaning or may be suggestive for difficulties in weaning. Criteria for initiating a weaning attempt include (selection): a left ventricular ejection fraction (EF) of at least 20%, pulsatile flow, normalized arterial lactate, a mean arterial pressure of at least 65–70 mmHg, low requirement of vasopressor or inotropic support, oxygen saturation nearly 95%, central venous oxygen concentration >60% and a low ventilatory support for normal lung ventilation and oxygenation while on VA–ECMO support. Weaning is initiated by gradually reducing VA–ECMO pump flow while monitoring cardiac function continuously. If signs of inadequate cardiac output or tissue perfusion, e.g., increasing blood lactate levels, are observed, the patient will be returned to higher VA–ECMO support. Once a minimal VA–ECMO support (<2 L per minute) has been established during the weaning process, ensuring hemodynamic stability, termination of the extracorporeal circulation will take place and the cannulas will be clamped. Immediate decannulation using access site closure devices such as Angioseal^®^ (TERUMO^®^, Somerset, NJ, USA) and/or ProGlide^®^ (Abbott Park, IL, USA) will be performed at the bedside for percutaneously placed cannulas. Central cannulation or surgical cutdown requires cannula removal in the operating room. After complete and successful weaning, continuous monitoring of cardiac output is necessary to ensure organ perfusion is maintained. Additional ongoing inotropic support may be required for certain patients. Patients unsuitable or unable for weaning will be considered for transplant or assist device implantation (LVAD).

#### 2.10.3. Cytokine Adsobers

The adsorbers that are currently in clinical use have already received CE–approval for medical devices [12]. In this study the CytoSorb^®^ adsorber (CE 0344, CytoSorbents Europe GmbH, Berlin, Germany) serves as medical device for the intervention group (Figure 4). CytoSorb^®^ is ISO 10993 biocompatible, meeting strict standards of hemocompatibility and biocompatibility, and is compatible with both systemic heparin and regional citrate anticoagulation. The CytoSorb^®^ is a single-use device and will not be reused. The functioning of cytokine adsorbers is very similar to a hemoperfusion therapy [12]. In detail, it is an extracorporeal cartridge made of a highly porous, bio-compatible, polystyrene-based polymer beads with a mean diameter of 450 μm each [12]. The total polymer surface is thus extremely large (>45,000 square meters) [12]. The cartridge is perfused with whole blood [12]. Each 300 mL cartridge is pre-filled with a sterile isotonic sodium chloride solution [12]. Within the polymer, excessive levels of inflammatory mediators, such as cytokines, interleukins, anaphylline toxins, as well as damage- and pathogen-associated molecular patterns, are irreversibly bound in a physico-chemical manner [12]. The removal of these substances is concentration–dependent, so that low (physiological) cytokine levels are not affected [12]. Mainly hydrophobic (water-insoluble) molecules can be removed up to a size of 55 kDa, a size range that covers most pro–inflammatory mediators, but remains non–specific [12,29]. The service life of a cartridge is up to 24 h and the adsorber is approved for blood flow rates between 100 and 700 mL/min, while a blood flow of at least 150 mL/min is recommended [12]. For the priming and integration of Cytosorb^®^ into the ECMO circuit, commercial sets are available. After purging the cytokine hemoadsorber with saline solution and establishing an activated partial thromboplastin time (aPTT) of 60–80 s/activated clotting time (ACT) of 160–210 s, a portion of blood will then be branched off from the ECMO tubing system right before passing through the oxygenator. It will then flow through the cartridge and be guided into the ECMO outflow cannula of the patient before entering the pump. These connector sets are designed to be cut off from the ECMO circuit in order to replace the cartridge after 24 h of use without any changes to the ECMO circuit. The extracorporeal circuit and the additional circuit for the adsorber/tube will be monitored continuously.
